## Abstract

**Background:** The early detection of developmental conditions such as autism is vital to ensure children can access appropriate and timely evidence-based supports, services, and interventions. Children who have undetected developmental conditions early in life are more likely to develop later health, developmental, learning, and behavioral issues, which in turn can have a cumulative effect over the life course.

**Methods:** The current protocol describes a multi-site, cluster randomized control trial comparing a developmental surveillance pathway for autism to usual care, using opportunistic visits to general practitioners (GPs). Units of randomization are GP clinics across two Australian states (New South Wales and Victoria), with thirty clinics within each state, each of which will aim to recruit approximately forty children aged between ~18- and 24-months, for a total of ~2,400 participants. Children will be randomized to two clusters; namely, an autism surveillance pathway (ASP) or surveillance as usual (SaU). The screening process for the ASP arm involves primary and secondary screenings for developmental concerns for autism, using both parent and GP reports and observations. Children in both arms who show signs of developmental concerns for autism will be offered a full developmental assessment by the research team at 24 months of age to determine the efficacy of developmental surveillance in successfully identifying children with autism.

**Trial Registration:** The trial is registered with ANZCTR (ACTRN12619001200178) and reporting of the trial results will be according to recommendations in the CONSORT Statement.

## Introduction

The increasing prevalence of developmental conditions such as autism, first evident in early childhood, can pose significant challenges to the individual, their family, and society if left undetected and unsupported (1, 2). It is estimated that over two hundred and fifty million children globally do not reach their developmental potential due to a lack of access to sufficient supports and services (3, 4). In Australia, around one in five children starting their first year of school are “developmentally vulnerable” with delays in one or more domains of development (5). Additionally, despite early signs of autism emerging within the first 2 years of life for most children (6), the average age of autism diagnosis in Australia is 4.1 years among children accessing intervention under the age of 7 years (7). Children who have undetected and unsupported developmental conditions early in life are more likely to develop later health issues, including adverse adult mental health outcomes (8, 9).

There is significant evidence that providing supports, services, and interventions early in the life course can enable children to reach their full potential (10). However, significant challenges and inequities remain in detecting children at high likelihood of developmental conditions such as autism sufficiently early to take advantage of neural plasticity of the developing brain through implementation of comprehensive, multimodal, evidence-based interventions (11). Specifically, early identification and optimal early intervention in the toddler, and preschool years for children with early signs of autism is critically important for optimizing outcomes. For example, it has been shown that only 8% of children who received a diagnosis of Autism Spectrum Disorder (ASD) at 2 years of age had comorbid Intellectual Disability (ID) when followed up at 9 years, while almost a quarter (24%) of those who received the diagnosis between 3- and 5- years were found to have co-morbid ID (12); this is highly significant, as the monetary cost of ASD *without* ID across an individual's lifespan is estimated to be US$1.4 million, while the cost of ASD *with* ID is almost doubled, at US $2.4 million (13). Further, children who begin school without developmental difficulties or delays will remain on educational trajectories that are enhanced in comparison to children who begin school with unaddressed developmental concerns (14–16).

Ongoing developmental surveillance offers opportunities to identify children with developmental differences reflecting early features of autism, in a systematic way through health and developmental promotion, and provide early intervention. Over the past three decades, data have emerged suggesting that developmental issues beginning in infancy and toddlerhood have the potential to affect key outcomes in the longitudinal trajectory (17, 18) and, the earlier intervention is commenced, the better the outcome (19). There is also increasing evidence to suggest that early detection and intervention is efficacious, cost-effective, and that it may be a way of decreasing health inequality, disparities, and breaking the cycles of intergenerational disadvantage (1, 20–22). However, it has been observed that, despite some parents having concerns about their child's development from a very early age, children who were diagnosed with ASD were identified later than children with developmental delay or intellectual disability (23). Such delay in diagnosis can also result in increased parental stress and significant delays in initiating early intervention which, as stated above, can result in less than optimal outcomes over time (24).

Whilst advances have been made in developing effective early interventions for ASD, significant barriers exist in accessing such intervention early within the period of greatest responsiveness to support and intervention (25). There are a few studies that have explored processes for the detection of developmental vulnerability in early life and barriers to accessing early intervention. One such study is the Watch Me Grow (WMG) program (26), conducted in a birth cohort of two thousand children in Sydney, Australia, in partnership with the New South Wales (NSW) state government health department. The WMG study (26–29) revealed that up to 30% of children are at developmental risk by their 18-month “well-child” check, but only 30–50% of these children attending primary health care (general practitioners—GPs, and child and family health nurses—CFHNs) have their developmental surveillance record completed. This is in keeping with the findings from a population health survey in NSW, Australia (30) that found that only around 66% of children attend “well-child” checks until around 12 months of age, and that this rate drops to 20% between 1 and 4 years of age. Thus, the period from 12 months to 5 years of age is a critical “silent” period for assessing a range of developmental and behavioral concerns, including speech and language difficulties and ASD. However, it is to be noted that across Australia there is considerable variability between states in children accessing developmental surveillance (26). For example, while NSW has a developmental surveillance attendance rate of 30% at 18 months (31), attendance is much higher in Victoria (VIC) at 74.2% (32).

Further, the WMG study found evidence of an “inverse care law,” whereby those at highest risk (such as children whose mothers were born overseas, or with lower maternal education and income levels) for developmental delay were the least likely to access the developmental surveillance program (27, 29). Qualitative analyses also indicated that facilitators to accessing developmental surveillance for families included proximity to the center, continuity of care, visits being combined with another recommended service (e.g., immunization) and language concordance by the provider (33). Access to good developmental surveillance programs could lead to better support for families, particularly those who have complex and multiple social risk factors.

The early detection of autism was investigated in Australia using Social Attention and Communication Surveillance (SACS) and its revised version (SACS-R) (34–37). A training program for universal developmental surveillance of autism was undertaken with maternal and child health nurses and early childhood educators, respectively. The program included education on the early behavioral markers for autism and the use of an evidence-based tool to monitor approximately thirty-four thousand children aged 8- to 24-months to identify those with a “high likelihood” of autism. Designed for use during routine developmental surveillance, the tool uses professional observations to monitor the child's development between 11- and 30-months of age using age-appropriate behavioral markers of autism (37). Children identified as having a “high likelihood” of autism were invited for developmental assessments by the research team, with six-monthly follow-ups and a “gold standard” diagnostic assessment at 24 months and 3.5 years of age. The SACS/SACS-R is currently the most accurate and sensitive tool for the early identification autism and related developmental conditions, such as developmental and/or language delay (psychometrics outlined in “Methods” section).

Currently there is considerable investment in disability services in Australia, with a new national program available for supporting those with a disability and their carers/families: the National Disability Insurance Scheme (NDIS) (38). The escalating costs, both financial and otherwise, of developmental conditions and particularly ASD has been highlighted by the fact that 29% of those entering the NDIS were doing so through a diagnosis of ASD (39). A significant proportion also have behavioral and emotional challenges, which, if not managed appropriately, can result in a lifetime of significant co-occurring mental health difficulties (33). This has led the Cooperative Research Centre for Living with Autism (Autism CRC) to provide funding support to carry out this study examining the implementation of a universal developmental surveillance program with a particular focus on ASD in the primary care setting. This study also aims to develop an integrated care pathway for follow up assessment, diagnostic determination, and referral to appropriate services, including secondary and tertiary services, in collaboration with the local health services as well as NDIS providers in the geographical area. This project will also help to evaluate the implementation of the recently launched National Health and Medical Research Council (NHMRC)-endorsed National Guideline for the Assessment and Diagnosis of Autism Spectrum Disorder in Australia (NAG) (40). Developed and published by the Autism CRC, with the financial support of the National Disability Insurance Agency (NDIA), the NAG aims to create greater consistency in diagnostic practices across Australia.

## Aims and Objectives

The overall objective of the project is to develop and evaluate a potentially sustainable approach to ASD detection within a developmental surveillance framework, in children aged 18–24 months using opportunistic GP clinic visits in the primary care setting. Specifically, this project will aim to examine whether, compared to Surveillance as Usual (SaU), an ASD Surveillance Pathway (ASP) will be associated with: (a) improved uptake and completion of developmental and autism surveillance; and (b) increased accuracy in identifying children at “high likelihood” of autism and related conditions, such as developmental and/or language delay. Secondary outcomes to be investigated include whether the ASD surveillance pathway will increase parental/caregiver engagement, health literacy, and satisfaction in accordance with the NAG, and increase GP awareness and utilization of developmental and autism surveillance tools and resources.

## Hypotheses

With regard to the primary outcomes, we hypothesize that, compared to SaU, the:

proportion of children completing autism developmental surveillance at the primary health care GP clinic will be increased in the ASP groupproportion of children correctly identified as being at “high likelihood” of autism, as evidenced by the comprehensive gold standard assessment results, will be increased in the ASP group.

Further, a qualitative component of the study will ascertain the parental/caregiver participation and experience in the program when followed up at 30-months-of-age. The study will also capture stakeholders' (including parents/caregivers and health professionals) perspectives of the barriers and enablers influencing the implementation of the NAG. The integrated model of developmental surveillance and referral used in the active arm of the intervention (ASP) will be compared to surveillance as usual (SaU) in terms of uptake of recommendations and service access and satisfaction, thereby informing the development of an integrated surveillance and care pathway in Australia. Thus, this study builds on existing state and national programs to identify barriers and develop mechanisms for accurate early detection of ASD in Australia.

## Methods and Analysis

### Study Design

A multi-site, cluster RCT with a qualitative component will be implemented (Figure 1). Using a minimization randomization procedure over size of GP clinic (<4 GPs or ≥4) and site (NSW or VIC), the participating GP clinics within the two Australian States (NSW and VIC) will be allocated to one of two arms:

Surveillance as Usual (SaU), representing current practice, orASD surveillance pathway (ASP), which will implement the “enhanced surveillance” protocol.

**Figure 1 F1:**
[figure not shown]
Study design.

### Participants and Setting

Within each state (NSW, VIC), approximately thirty GP clinic “clusters” will be recruited (approximately sixty in total). Children aged approximately 18- to 24-months attending the GP clinics will then be recruited as part of each cluster. GP clinics will be recruited through various methods including using Primary Health Networks to distribute study information. GPs and, in some instances, the clinic practice nurse/s (PN) will be recruited, with each clinic having at least one GP consenting to recruit children to the study. A “universal surveillance” approach to recruitment will be implemented, such that any toddler between the eligible ages attending an appointment at the clinic for any reason, including for an immunization, can be recruited to the study. Approximately forty children will be recruited from each GP clinics, creating a total child sample size of ~2,400. For the qualitative component of the study, parents of children identified with a developmental concern and approximately twenty GPs and/or PNs will be recruited.

### Phase 1 - GP Clinic Visit

Prior to commencing the study, GPs and PNs will receive training on the study procedure and use of the study iPad and weblink, and, for those in the ASP group, the study screening tools. Clinic reception staff will also receive training on the study procedure and participant recruitment. Potential participants will be identified by reception staff when the child presents for their GP appointment, by staff checking the child's age in the patient record. Reception staff will offer the child's parent/caregiver information on the study in the form of a study flyer. Clinics will also have study posters with the same information on display. Parents/caregivers who would like to participate in the study will be asked to complete the participant information and consent form and demographic questions on the study iPad (or via their own mobile device), with those in the ASP group also completing developmental screening questionnaires. Once the parent/caregiver completes the developmental screening questionnaires and submits the response using the weblink, the GP receives the results via email or the Salesforce platform so that this information is available to the GP at the point of care during the consultation.

Table 1 summarizes clinical and behavioral measures and assessments for both ASP and SaU pathways. Measures will be taken at various points in the trial to allow appropriate comparisons between the groups (see Figure 1 and Table 1). Client-facing documents such as the information sheet, consent form, and screening questionnaires have been translated into Arabic, Chinese (Mandarin), and Vietnamese, the most common languages spoken by culturally and linguistically diverse (CALD) families in our study locations.

**Table 1 T1:** Study Flow Chart.

**Time points**	**Age (months)**	**Location**		**Groups and tools**		
1	18–24		**Autism surveillance pathway**		**Surveillance as usual**	
			Service data		Service data	
		Waiting Room	Consent Demographics LTSAE; PEDS Q-CHAT-10		Consent Demographics	
		Doctor's Office	SACS Online (GP completes)		Brief online form to inform research team of high ASD risk, type of concern, screening method used, and referrals and recommendation provided	
			**Developmental concerns (any)**	**No concerns**		
		Waiting Room	ASQ:SE (option to complete at home)	–	–	
			**High ASD risk**	**Low ASD risk 10% complete**	**High ASD risk**	**Low ASD risk 10% complete**
2	24	Research Site	Demographics	Demographics	Demographics	Demographics
			ADOS-2	ADOS-2	ADOS-2	ADOS-2
			ADI-R	ADI-R	ADI-R	ADI-R
			MSEL	MSEL	MSEL	MSEL
			SEQ	SEQ	SEQ	SEQ
			ITSP	ITSP	ITSP	ITSP
			VABS-3	VABS-3	VABS-3	VABS-3
3	30	Online	SRS-2	SRS-2	SRS-2	SRS-2
			Semi-structured questionnaire		Semi-structured questionnaire	

*ADOS-2, Autism Diagnostic Observation Schedule Second Edition; ASD, Autism Spectrum Disorder; ADI-R, Autism Diagnostic Interview – Revised; ASQ:SE, Ages and Stages Questionnaire; ITSP, Infant Toddler Sensory Profile; LTSAE, Learn the Signs Act Early; MSEL, Mullen Scales of Early Learning; PEDS, Parents' Evaluation of Developmental Status; Q-CHAT, Quantitative Checklist for Autism in Toddlers; SACS-Online, Social Attention and Communication Surveillance – online; SEQ, Sensory Experiences Questionnaire - short form; SRS-2, Social Responsiveness Scale; VABS-3, Vineland Adaptive Behavior Scale 3rd Edition*.

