### Phase 4 – Evaluation

GP clinic audits will be conducted to gather data on the number of children in the eligible age group seen during the recruitment period, the number of children where the developmental surveillance was conducted, and the number of children referred for developmental concerns, as per current practice. The data will be obtained using the clinics' client management software to generate deidentified reports on the numbers of children in the eligible age group seen during the recruitment period.

We will conduct qualitative interviews with 10 parent/caregiver and 10 professional (GPs/PNs) participants at each site in order to explore the enablers and barriers for completion of universal developmental and autism surveillance checks within the GP setting as well as about the utilization of the NAG, access to referral pathways and early interventions.

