### Statistical Analysis

#### Quantitative Analysis

The entire raw dataset will be provided to an independent biostatistician, along with the study protocol and the pre-specified statistical analysis plan, who will conduct an independent analysis of the raw data. Details of this independent statistical analysis, as well as the name and academic institution of the independent statistician and whether compensation or funding was received for conducting the analyses, will be included in the publication of the results of the study.

Descriptive statistics for outcome measures (percentage, mean, and SD) and psychometric properties of the measures (reliability, Cronbach's α) will be reported. Descriptive statistics for all parental socio-demographic will also be presented, with the expectation of no group differences. We will compare the differences between the control arm (SaU) and the intervention arm (ASP) for the following primary outcomes:

(1a). the uptake of autism developmental surveillance as indicated by the proportion of children who participated in the program;(1b). the proportion of children correctly identified by the GPs as being at “high likelihood” of autism, and later confirmed as having ASD through the “gold standard” assessment.(2) the proportion of children in both groups who received referrals following identification of developmental concerns;(3) the access and utilization of child health and developmental services will be ascertained based on the uptake of recommendations as assessed at the 30-month follow up.

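### Children are recruited by opt-in after the clinic's arm is known and the consent sitting differs by arm, so 1b among recruited children can mix the pathway effect with case mix

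*Protocol article*

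**What the plan says.** The order of events comes from three sections of the protocol article.

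- **Allocation.** Under Study Design, "the participating GP clinics within the two Australian States (NSW and VIC) will be allocated to one of two arms", by minimisation on clinic size and state.
- **Children come later.** Under Participants and Setting, "Children aged approximately 18- to 24-months attending the GP clinics will then be recruited as part of each cluster".
- **Training by arm comes first.** Under Phase 1 - GP Clinic Visit, GPs and practice nurses are trained before the study starts in the procedure "and, for those in the ASP group, the study screening tools".
- **Approach and opt-in.** In the same section, "Potential participants will be identified by reception staff when the child presents for their GP appointment", using the age in the record. Parents who wish to take part then consent on the iPad or their own device, "with those in the ASP group also completing developmental screening questionnaires".

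Table 1 and the two Procedures sections agree on the contrast. The ASP sitting consists of consent, demographics, LTSAE, PEDS and Q-CHAT-10, with results passed to the GP. The SaU sitting consists of consent and demographics.

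Outcome 1b, under Quantitative Analysis, is the proportion of children whom GPs correctly flag and whom the 24-month assessment later confirms. The article does not state its denominator. The same section presents parental socio-demographics "with the expectation of no group differences". Phase 4 – Evaluation plans a clinic audit that counts "the number of children in the eligible age group seen during the recruitment period".

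**The concern.** In a cluster trial, randomisation protects the comparison of all eligible children attending the clinics. It protects the comparison of recruited children only if the chance of consenting depends on the child's condition in the same way in both arms. That is in doubt here, because families opt in at a clinic whose arm is already fixed and known, and what they take on at that sitting differs by arm. The article describes no recruiter unaware of the arm, no identification of children before allocation, and no statement that the offer reads the same in both arms.

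The article's Introduction gives reasons to expect that consent is related to the child's status, and they point in opposite directions. Some parents are worried very early, which could draw them to an offer of screening. Children at highest risk were also the least likely to reach a surveillance programme.

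Outcome 1b is at stake. Over recruited children, it is the product of how many autistic children were recruited and how many of those were found. A difference in the first factor would be read as an effect on the second.

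**Working it through.** The article gives no autism prevalence, consent rate or detection rate, so there is no figure of its own on this point to reproduce. The sample size statement is in standard deviations and does not bear on it. The following is an illustration.

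**Inputs**
- From the article: 2,400 children in total; risk difference as the effect measure.
- Assumed: 1,200 children per arm; 1b taken over recruited children; autism share p among SaU consenters; share d detected and confirmed, equal in both arms, so that there is no pathway effect; relative consent ratio r, meaning how much more likely families of autistic children are than other families to consent in ASP, relative to the same comparison in SaU.

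**Formulas**
- Autism share among ASP consenters = p·r / (p·r + 1 − p)
- 1b in SaU = p·d; 1b in ASP = (ASP autism share)·d

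**No pathway effect: p = 2%, d = 50%**

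| r | ASP autism share | 1b ASP | 1b SaU | Spurious RD (points) | Children per 1,200, ASP v SaU | Ratio |
|---|---|---|---|---|---|---|
| 1.25 | 0.025/1.005 = 2.49% | 1.24% | 1.00% | +0.24 | 14.9 v 12.0 | 1.24 |
| 1.5 | 0.030/1.010 = 2.97% | 1.49% | 1.00% | +0.49 | 17.8 v 12.0 | 1.49 |
| 2.0 | 0.040/1.020 = 3.92% | 1.96% | 1.00% | +0.96 | 23.5 v 12.0 | 1.96 |

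Ignoring clustering, the chance of a significant result in these three cases is about 8%, 19% and 50%, where it should be about 5%. Over p from 1% to 3%, d from 30% to 80% and r from 1.25 to 2, the spurious difference runs from +0.07 to +2.26 points.

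**True effect present: p = 2%, detection 30% in SaU and 60% in ASP**
- r = 1: 0.02 × 0.60 − 0.02 × 0.30 = +0.60 points (the true effect).
- r = 1.5: 0.0297 × 0.60 − 0.0060 = +1.18 points.
- r = 0.75: ASP share 0.015/0.995 = 1.51%; 0.0151 × 0.60 − 0.0060 = +0.30 points.

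The same mechanism can therefore double the effect or halve it.

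**Would the audit denominator repair 1b?** Per age-eligible child seen, 1b = (autism share among eligible) × (consent rate in families of autistic children) × d. With the first and last factors equal between arms, the ASP to SaU ratio equals the ratio of those consent rates. If that ratio is 1.5, the audit-based 1b is still 1.5 times as high in ASP. The audit yields deidentified counts without autism status, so the numerator still contains only consenting children.

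**The case against.** Much of the case on the other side stands, and it limits the claim.

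- **SaU parents also have a reason to join.** The Abstract and the Phase 2 Procedure offer the 24-month assessment to flagged children in both arms. The three extra waiting-room forms could also deter some ASP families. A reader might infer that worried parents have a motive only in ASP, and so that 1b must be inflated there. The text does not support that.
- **Flyer, poster and consent wording are not shown.** The article mentions no arm-specific versions, and Table 1 lists consent ahead of the questionnaires. Part of the remedy may already be in place. Arm-specific training is stated only for GPs and practice nurses; that reception staff know the arm is inferred from the procedures they run.
- **The balance statement is narrower than it looks.** "with the expectation of no group differences" refers to parental socio-demographics. It is not a claim about autism case mix and should not be read as one.
- **The denominator of 1b is open.** If 1b were detection among autistic children, recruiting more of them would not by itself move it, and the figures above would not apply. The recruited sample is the natural reading, because only enrolled children have a study risk status and a 24-month assessment.
- **Some safeguards exist.** Children are identified by age, adjustment for gender, maternal education and socioeconomic status is foreseen, 10% of screen negatives are assessed in both arms, and the SRS-2 is collected on all recruited children at 30 months.

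These safeguards are partial. Identification by age governs who is approached, not who consents. The named covariates do not include prior parental concern. The 10% sample is at most about 120 children per arm; with p = 2% and d = 50%, roughly 1% of screen negatives would be missed cases, or about one child, too few to compare prevalence between arms. The SRS-2 is measured after the intervention and is not planned as a check on selection.

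**Conclusion.** The point holds as a design weakness of moderate weight. The article supports three facts: opt-in follows arm-specific preparation of the clinic, the consent sitting differs by arm, and nothing described makes the offer neutral. Randomisation therefore does not by itself protect a comparison of recruited children on 1b.

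The document does not support a direction or a size. The figure of +0.24 to +0.49 points rests on assumed values for prevalence, detection and consent ratio, on an equal split of children between arms, and on 1b being taken over recruited children. It shows only that a modest consent difference could be of the same order as a plausible true effect: +0.49 points from selection alone at r = 1.5, against +0.60 points for a doubling of detection from 30% to 60%. With a ratio below 1, the same mechanism would mask a benefit. It would be wrong to conclude that the trial is biased towards ASP, or that the clinic audit cures the problem by supplying a denominator.

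**What to change.** 1. **Make the offer arm-neutral.** Use an identical flyer, poster, consent text (describing both possibilities) and demographic page in both arms, and open the ASP questionnaires only after consent is submitted. If the current materials already do this, say so.
2. **Show who was recruited.** From the planned audit, report recruited over age-eligible children by arm and by clinic, and compare consenters' characteristics between arms.
3. **Name the covariates in advance.** Adjust 1b for consent-time covariates chosen beforehand, for example child sex, maternal education and socioeconomic status, plus the minimisation factors (clinic size and state). This replaces choosing covariates because they differ significantly, as the Statistical Analysis section now allows. Confirm that the brief demographic form records them.
4. **Optional sensitivity analysis.** Report 1b per age-eligible child at clinic level, stating that it does not remove selection because its numerator includes only consenting children.

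The cost is a change in form order on the iPad, revised wording if the materials now differ by arm, and a small amount of extra analysis on data already planned. Item 1 helps only families approached after the change; items 2 to 4 remain possible whatever stage recruitment has reached. With about 27 to 30 events in total in the illustration (12.0 + 14.9 to 12.0 + 17.8), the covariate list must be short, and measured covariates cannot remove all selection.
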